# Cognitive aids for people with early stage dementia versus treatment as usual (Dementia Early Stage Cognitive Aids New Trial (DESCANT)): study protocol for a randomised controlled trial

**DOI:** 10.1186/s13063-018-2933-8

**Published:** 2018-10-10

**Keywords:** Early-stage dementia, Memory aids, Community, Psychosocial outcomes, Quality of life, Effectiveness, Cost-effectiveness, Pragmatic randomised trial, Process evaluation

## Abstract

**Background:**

There is a growing need for an evidence-based approach to home support for people with dementia and their carers following diagnosis but research on the effectiveness and cost-effectiveness of different approaches is sparse. The Dementia Early Stage Cognitive Aids New Trial (DESCANT) will evaluate the clinical and cost-effectiveness of a range of memory aids, training and support to people with mild to moderate dementia and their carers at home and compares that intervention with treatment as usual.

**Methods/design:**

This is a multi-site, pragmatic randomised trial preceded by a feasibility study and internal pilot. We aim to allocate at random 360 pairs comprising a person with mild to moderate dementia and an identified carer between the DESCANT intervention and treatment as usual. We assess participants at baseline, 13 and 26 weeks. The primary outcome measure is the Bristol Activities of Daily Living Scale; other participant outcomes include cognition, quality of life, activities of daily living and social networking; carer outcomes include quality of life, sense of competence and mental health. To enhance this quantitative evaluation we are conducting a qualitative component and a process evaluation to assess the implementation process and identify contextual factors associated with variation.

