### Sample size

An analysable sample of 360 (180 in each group) across participating Trusts would yield 80% power to detect an effect size (standardised mean difference) of 0.30 on BADLS when using a two-sided significance level of 5%. To allow for 25% attrition (estimated from previous similar studies) between baseline and final interviews the aim is to recruit 480 randomised pairs of people with mild to moderate dementia and an identified carer.

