### Statistical analysis

Analysis will follow a defined statistical analysis plan approved by the DMEC before data are accessed. Baseline characteristics of participants will be presented. Continuous variables will be reported by means and standard deviations and categorical variables by counts and percentages. Analyses by treatment allocated will estimate the effect of the intervention on participants, using analysis of covariance to adjust for baseline differences in demographic characteristics, comorbidities, time since first attendance at memory clinic or equivalent and for the interval until follow up. Primary analysis will focus on BADLS scores at 26 weeks. Secondary analysis will take account of the content of, and adherence to, the intervention to explore the effect of compliance on BADLS scores.

To explore whether people with dementia who have particular characteristics are more likely to use specific aids, logistic regression will be used. To identify which participants are more likely to benefit from this intervention, linear regression will be used to relate change in BADLS scores at 26 weeks to similar covariates.

Whether the inevitable missing data cause bias will be investigated. If predictors of missing data are identified that are related to outcomes, multiple imputation to adjust for these biases will be used.

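### The abstract sets 360 pairs as the number to randomise, the sample-size section 480; randomising 360 with the planned 25% attrition gives about 69% power, not 80%

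*Protocol article*

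**What the plan says.** The abstract of the protocol article, under Methods/design, states: "We aim to allocate at random 360 pairs comprising a person with mild to moderate dementia and an identified carer".

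The Sample size section gives the number 360 a different meaning: "An analysable sample of 360 (180 in each group) across participating Trusts would yield 80% power". The effect size is a standardised mean difference of 0.30 on BADLS, tested at a two-sided 5% level. The section then adds an allowance for loss, "To allow for 25% attrition (estimated from previous similar studies) between baseline and final interviews", and ends with the recruitment target: "the aim is to recruit 480 randomised pairs of people with mild to moderate dementia and an identified carer".

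The Statistical analysis section fixes the time point to which these numbers apply: "Primary analysis will focus on BADLS scores at 26 weeks".

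**The concern.** Both sentences state an aim, both count randomised pairs, and both describe the same population, yet one says 360 and the other 480. They cannot both be the randomisation target. The abstract's figure equals the Sample size section's analysable figure, so it looks as if a number meant for the end of follow-up has been attached to randomisation.

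The target decides when recruitment stops and how the steering and monitoring committees judge progress. It is also the figure against which readers will later decide whether the trial reached its planned size. The Trial status section says recruitment was still open and due to run through 2018, so the number was live at publication. Anyone who works from the abstract would stop 120 pairs short, a quarter of the 480, and the 80% power claim would no longer describe the trial.

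**Working it through.** **Inputs, all from the protocol article**

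- Randomised, per the abstract: 360 pairs.
- Analysable, per Sample size: 360, that is 180 per group.
- Effect size d = 0.30 (SD = 1 on this scale), power 80%, two-sided alpha 0.05.
- Attrition: 25%.
- Randomised, per Sample size: 480 pairs.

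**Step 1. Reproduce the plan's own figures.** For two equal groups and a continuous outcome, the normal approximation gives

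n per group = 2 × (1.960 + 0.842)² / 0.30² ≈ 174.4, rounded up to 175 (350 in total).

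The exact two-sample t test (noncentral t) needs 176 per group, or 352 in total. The plan's 360 is this figure rounded up.

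Power with 180 per group: the noncentrality is 0.30 × √(180/2) = 2.846, which gives 81.2% by the normal approximation and 81.0% by the t test. The plan calls this 80%.

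Inflation for attrition: 360 / (1 − 0.25) = 480, an exact match. The Sample size section is therefore internally consistent.

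**Step 2. Take the abstract at its word.** With 360 randomised and the same 25% attrition:

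- Analysable: 360 × 0.75 = 270, that is 135 per group.
- Noncentrality: 0.30 × √(135/2) = 2.465.
- Power: 69.3% (normal approximation), 69.0% (t test).

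**Step 3. Effect detectable with 80% power.** By the normal approximation this is (1.960 + 0.842) × √(2/n).

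| Randomised | Analysable per group | Power at d = 0.30 (t test) | d detectable with 80% power (t test) |
|---|---|---|---|
| 480 | 180 | 81.0% | 0.296 |
| 360 | 135 | 69.0% | 0.342 |

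**Step 4. How far the result depends on 25%.** With 360 randomised, the t test gives:

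| Attrition | Analysable per group | Power |
|---|---|---|
| 25% | 135 | 69% |
| 20% | 144 | 72% |
| 15% | 153 | 74% |
| 10% | 162 | 77% |
| 0% | 180 | 81% |

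Since 352 analysable pairs are needed for 80%, 360 randomised would suffice only if no more than 8 pairs were lost (8/360 = 2.2%).

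**Step 5. Look for a reconciling statement.** The Design section reports that the pilot's only adjustment was to shorten follow-up from 12 to 6 months, partly so that recruitment targets could be met. It gives no lower target and does not revise the attrition rate. Trial status gives no recruitment number. The flowchart (Fig. 1) is not reproduced in the text available here; whatever it shows, the two sentences would still disagree.

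**The case against.** The strongest reply is that this is a labelling slip in an abstract. The section that sets the sample size is complete and correct, no calculation in the article fails, and the abstract's number is exactly the analysable number. On that reading nothing about the design or its power changes. Recruitment is run by a trials unit with steering and monitoring committees, and there is no sign that anyone recruits from the abstract. This is the likelier explanation, and the point is better described as an inconsistency than as a miscalculation. But the article does not show which figure is current. It does say that recruitment pressure was one reason for shortening follow-up, so a reader cannot rule out that 360 had become the working target.

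A second reply is that 69% depends on assumptions: that 360 is the true target, that the full 25% is lost, and that the comparison is unadjusted. That is right. The 25% is the plan's own planning figure, although the article does not say whether it refers to 12 or 6 months of follow-up. The planned analysis of covariance could recover some power. If the covariates correlated 0.3 with the outcome, power with 135 per group would be about 73%; at 0.5 it would be about 81%. Both correlations are assumptions. The article gives none, does not name baseline BADLS among the covariates, and takes no credit for adjustment in its sample size.

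A third reply is that 480 is not the only number that works, since 352/0.75 is about 470. That is true, but 470 is not one of the stated targets. Of the two that are stated, only 480 delivers the claimed power under the stated attrition.

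**Conclusion.** The concern holds. The article states two incompatible randomisation targets, 360 and 480, and this contradiction depends on no assumption. The Sample size section's inputs support 480.

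The loss of power is conditional. If 360 is the true target, 25% are lost and no credit is taken for covariate adjustment, then 270 pairs are analysable, power at 0.30 is about 69%, and 80% power is reached only at about 0.34 SD. If 480 is the target, the power statement stands and only the abstract is wrong. Because the figure governs recruitment in a trial that was still open, it should be corrected whichever number is right.

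**What to change.** First confirm with the sponsor and the trials unit which target is in force.

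- **If 480:** change the abstract to say that 480 pairs will be randomised in order to leave 360 analysable at 26 weeks. This is one sentence, with no change to design, cost or recruitment.
- **If 360:** keep the abstract and rewrite the Sample size section to give 270 analysable pairs (135 per group) after 25% attrition, with about 69% power at 0.30 and 80% power at about 0.34. If a lower attrition rate or a gain from covariate adjustment is used to justify 360, state the assumed value and its source. This is a short restatement, but it acknowledges lower power than the article now claims.

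In either case, check that the flowchart and the registry entry carry the same number.

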**Discussion:**

The DESCANT intervention reflects current policy to enhance the capabilities of people with dementia after diagnosis and their carers. If it is clinically and cost-effective, its modest nature and cost will enhance the likelihood of it being incorporated into mainstream practice.

**Trial registration:**

Current Controlled Trials, ISRCTN12591717. Registered on 29 July 2016.

Protocol number**:** 31288: North West - Haydock Research Ethics Committee, 20/06/2016, ref.: 16/NW/0389.

## Background

Worldwide there were about 47 million people living with dementia in 2015; since there is no cure the costs associated with the condition will increase [1]. In England there is considerable interest in achieving early diagnosis and treatment of dementia through memory services, and providing a spectrum of care including interventions and support after diagnosis [2–4]. Diagnosis can help people with dementia and their carers to receive the treatment, care and support (pharmacological, psychosocial, social and emotional) to enable them to manage this condition.

Rigorous research is required to inform the choice of treatment options [5]. However robust evaluation of the use of common memory aids, like calendars, clocks, whiteboards with electric timers and “post-it” note dispensers, by those diagnosed with early dementia is lacking despite being widely recommended [6, 7] . A Cochrane review [8] identified several studies that reported the utility of memory aids or associated memory training, but they were small scale, highlighting the need for a larger study [9–11].

This trial aims to design, implement and evaluate an intervention to support people with early-stage dementia and their carers in the use of memory aids at home. It is one of nine distinct, but linked, projects within a research programme designed to discern different models of support in England and evaluate cost-effectiveness in providing care for people with dementia and their carers at home; the Personal Social Services Research Unit (PSSRU) at the University of Manchester is leading this trial.

Figure 1 shows a Consolidated Standards of Reporting Trials (CONSORT) flowchart of the trial.

**Fig. 1 Fig1:**
[figure not shown]
DESCANT trial flowchart

## Methods/design

### Governance arrangements

The Programme Steering Committee (PSC) oversees the programme of which this trial is part. It comprises representatives of patients and public, old age psychiatry, psychology, health services research and biostatistics, and works to an agreed Charter. It also acts as the independent Trial Steering Group.

This trial has been adopted by the Swansea Trials Unit (STU) and will be conducted according to its standard operating procedures. The Trial Management Group comprises PSSRU staff at the University of Manchester, and it monitors compliance and reports to NHS Trusts, oversees and resolves operational issues in partnership with colleagues at STU, and reports to the Data Monitoring and Ethics Committee (DMEC) and the funder, the National Institute of Health Research (NIHR). The DMEC meets at least annually and reports to the PSC; the chair is a geriatrician with a particular interest in dementia, and their charter reflects established practice [12]. Only the DMEC have access through the Trial Data Manager to unblinded data before the trial ends; it will unblind the DESCANT analysis team only after approving the blinded primary analysis.

The Public, Patient and Carer Reference Group (PPCRG) comprises a regular meeting of 6 members resident in North West England and a Lay Advisory Panel of 20 members across the country, established through Together in Dementia Everyday (TIDE).

### Design

This is a multi-site, pragmatic randomised trial to evaluate the effectiveness and cost-effectiveness of memory aids delivered by Dementia Support Practitioners (DSPs) to people with early-stage dementia relative to treatment as usual (TAU). Pairs of people with mild to moderate dementia and an identified carer will be recruited and allocated at random between the comparator group receiving TAU plus dementia guide [13] and the intervention group receiving TAU plus the DESCANT intervention. The primary outcome measure is the Bristol Activities of Daily Living Scale (BADLS) [14], measured at 13 and 26 weeks (primary end point) after baseline.

To ensure intervention and methods work in practice, a feasibility study and internal pilot was conducted with 40 participants, recruited from two settings in equal numbers. The Acceptance Checklist for Clinical Effectiveness Pilot Trials (ACCEPT) criteria [15] was adapted to assess whether the intervention and the trial protocol work in practice, and the DMEC had accepted these criteria. The only adjustments suggested by the pilot was to reduce the length of follow up from 12 to 6 months in the main study to enable the recruitment targets to be met and reflect the realistic goal of improving BADLS scores over 6 months. Therefore, the pilot data will be included, adjusted to reflect this change in the main analysis. This modification, approved by the University of Manchester as Sponsor, was communicated to the National Research Ethics Service who approved the original protocol (reference 15/NW/0822), sites and participants.

### Intervention

The manualised intervention adds specialist equipment and advice by trained DSPs to TAU. It provides up to 6 hours contact with a DSP for the person with dementia and the identified carer (jointly referred to as participants). DSPs design and deliver a package of memory aids up to a maximum of £150 for the person with dementia to use at home. The package for each depends on their needs, preferences and existing use of memory aids. DSPs also advise on improving everyday memory skills and on using these aids to reduce memory lapses. The follow-up sessions address queries from participants and record whether aids are appropriate to the identified goals and needs and used accordingly. Further details about the implementation of the intervention are provided in Fig. 2.

**Fig. 2 Fig2:**
[figure not shown]
DESCANT intervention. Source: [62]

#### Treatment as usual

TAU comprises help from memory clinic staff, post diagnostic counselling and advice, and specialist follow up as appropriate. Participants in the comparator group also receive a general guide to dementia for patients and carers [13].

### Setting

The study runs in three National Health Service (NHS) Trusts in England, and more may follow. To be eligible participating Trusts must provide a memory service, a health-based resource providing early diagnosis and support for people with dementia and their carers. They must also identify a local Principal Investigator (PI), obtain support from their local Research and Development department and Clinical Research Network (CRN) to complete the research activities described in this protocol, and employ appropriately experienced persons as DSPs.

Participants will be recruited primarily from memory services. “Join Dementia Research,” an on-line self-registration service enabling volunteers with memory problems or dementia and their carers to register their interest in taking part in research, will also be used as a recruitment tool.

### Participants

#### Inclusion criteria

Index people with dementia must be aged 50 years or more; cared for by a trial memory clinic or equivalent; within one year of their first attendance at that clinic for dementia; physically able to engage with the intervention (as judged from clinical records); clinically able to do so, as judged by a responsible clinician and have dementia of mild to moderate severity. At baseline, they must live in their own home or share a home with a relative. They must have an identified carer, defined as the primary person who feels responsible for and supports them. This could be a family member, a close friend or a neighbour.

### Recruitment

#### Sites

Sites will be recruited via professional and research networks, including the UK NIHR Clinical Research Network (CRN). Participating Trusts will identify memory clinics for inclusion in the study. Each site will confirm their capacity to undertake the trial by completing the Health Research Authority Statement of Activities as a formal agreement with the Sponsor.

#### People with dementia and their carers

Clinical staff in participating Trusts are briefed about the trial and provided with participant information sheets (PISs) for potential participants. They will complete a screening schedule to check eligibility, give the PIS to participants, and seek oral consent to refer them to the DESCANT team. Recruitment, documents and processes were designed following guidance from the PPCRG on language and format, to ensure that those with cognitive impairment are fully informed and engaged in the decision to take part.

#### Consent process

Clinical staff within agencies will introduce the study to participants, provide them with PISs and obtain their consent to contact by a member of the research team. Before conducting the interview, researchers explain the study to participants and obtain their formal consent. Guided by the Mental Capacity Act 2005 [16], it is judged that people with mild to moderate dementia approached in this way have capacity to provide informed consent, given sufficient time to decide.

Participants may withdraw from the trial at any time for any reason. If they withdraw, a reason will be recorded unless they choose not to provide one. PIs may also withdraw people with dementia from the trial if they feel it is no longer in their best interest to continue. Unless participants request otherwise, data collected before withdrawal will be retained for analysis. Each site maintains a log of people who satisfy the inclusion criteria but are not recruited, including demographic details and reasons for not consenting to participate if given.

### Outcome measures

The schedule of outcome measures and assessment points are provided in Fig. 3.

**Fig. 3 Fig3:**
[figure not shown]
Schedule of enrolment, interventions and assessment points. BADLS: Bristol Activities of Daily Living Scale; CASP-19: Control, Autonomy, Self-realisation and Pleasure 19-item measure of quality of life; CDRS: Clinical Dementia Rating Scale; DEMQOL: Dementia Quality of Life scale; ICECAP-O: ICEpop (Investigating Choice Experiments for the Preferences of Older People) CAPability measure for Older people; LSNS-R: Lubben Social Network Scale - Revised; PANT: Practitioner Assessment of Network Type; R-IDDD: Revised Interview for Deterioration in Daily living activites in Dementia; S-MMSE: Standardised Mini-Mental State Examination; GHQ-12: General Health Questionnaire; SSCQ: Short Sense of Competence Questionnaire; CSRI: Client Service Receipt Inventory; RUD: Resource Utilisation in Dementia. Completion by 1 = carer; 2 = person with dementia; 3 = interviewer; 4 = either person with dementia or carer. Intervention A = Comparator group; Intervention B = Intervention Group

#### Primary outcome measure

##### Bristol Activities of Daily Living Scale

This assesses the independence of the person with dementia in activities of daily living [14]. As they may not always be aware of their deficits, carers assess these. The measure captures basic and instrumental abilities including dressing, bathing, food preparation and use of the telephone. It is valid and reliable and responsive to change over time [17]. Therefore, it is appropriate to evaluate a practical intervention designed to extend a person’s competence in daily living.

#### Secondary outcome measures for persons with dementia

##### Cognition (two measures)

The Standardised Mini-Mental State Examination (S-MMSE) is a brief widely used self-completed test of cognitive function with good validity and reliability, which measures the severity of cognitive symptoms of dementia [18]. The Clinical Dementia Rating (CDR) is an interviewer-completed scale to indicate level of impairment in six domains [19].

##### Quality of life (three measures)

Investigating Choice Experiments for the Preferences of Older People Capability measure for Older people (ICECAP-O) measures quality of life in older people across five domains [20]. The control, autonomy, self-realisation and pleasure 19-item measure (CASP-19), measures quality of life in older people across another four domains [21, 22]. Both these measures are self-completed by the person with dementia. The Dementia Quality of Life scale (DEMQOL) measures five domains of quality of life in dementia and has good validity and reliability [23]; either the person with dementia completes this or the carer completes a proxy version.

##### Activities of daily living

The Revised Interview for Deterioration in Daily living activities in Dementia (R-IDDD) enables carers to rate patients’ initiative and performance of daily living activities [24, 25].

